#### Parent measures

Postoperative pain: With the Postoperative Pain Measure for Parents (PPMP),^62^ parents can assess and estimate their child’s postoperative pain. The checklist includes 15 items where the parents select ‘yes’ (=1 point) or ‘no’ (=0 points) as to whether the child exhibits pain-related behaviour, with higher scores indicating more postoperative pain.

Fear of Pain Questionnaire: The Parent FOPQ^35^ is a 23-item self-report inventory to reflect a parent’s own fear associated with their child’s pain experience. Parents are asked to rate each item on a Likert scale from 0 (=strongly disagree) to 4 (=strongly agree). A higher total score indicates higher fear of pain.

Symptoms of anxiety and depression: The Hospital Anxiety and Depression Scale^63^ is a widely used measure of psychological distress, and indicates the presence of symptoms of depression (seven items) and anxiety (seven items) over a 1-week period. The 14 items are rated on a 4-point Likert scale ranging from 0 to 3, with higher scores indicate greater symptom severity.

Sensory processing sensitivity: The Highly Sensitive Person Scale^64 65^ is a 12-item self-reported questionnaire, and participants are asked to rate each item on a Likert scale from 1 (=strongly disagree) to 7 (=strongly agree). In addition to a total score, three subscales can be calculated, as for the HSC Scale: Low Sensory Threshold, Ease of Excitation and Aesthetic Sensitivity. Higher scores reflect higher sensitivity.

Emotion regulation: The ERQ^31^ assesses the habitual use of two emotion regulation strategies, namely cognitive reappraisal (six items) and expressive suppression (four items). The 10 self-reported items are rated on a 7-point Likert scale ranging from 1 (=strongly disagree) to 7 (=strongly agree). Higher scores indicate higher usage of the respective strategy.

Well-being: Parental well-being will be measured using he WHO-5 index.^66^ It consists of five items that are rated on a 6-point Likert scale ranging from 0 (=never) to 5 (=always), indicating how often participants have felt in ‘good spirits’, ‘active’, ‘relaxed’, etc over the course of the last 2 weeks. Higher scores indicate more well-being.

### Primary outcome

The primary endpoint is CPSP at FU 1. CPSP is defined as greater than minimal pain (pain intensity ≥3) on more than 50% of days as measured by daily diary over 7 days, and impairment in health-related quality of life (score of ≤74.9 on the PedsQL,^59^ ie, 1 SD below the population mean based on normative US data). The combination of pain and quality of life measures will result in a binary variable (CPSP yes/no). This measurement of CPSP is supported by previous research,^6 67 68^ and a modified definition of CPSP by the International Association for the Study of Pain.^69^

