## Introduction

Chronic postsurgical pain (CPSP) is defined as chronic pain that persists over time (at least 3 months) following a surgical procedure and that has a significant impact on physical and psychosocial quality of life.^1 2^ Meta-analytical estimates in children and adolescents describe that around 25% of paediatric patients undergoing major surgery report chronic pain 3–12 months after surgery.^2^ Highest pain intensity ratings are observed in 2 weeks following surgery, with a steady decrease afterwards over the following 6 months,^3^ and pain ratings 2 weeks after surgery have been shown to predict the development of moderate to severe pain 1 year later.^4 5^ Further, most children and adolescents experience decreases in their physical activity levels following surgery, and it has been suggested that objectively monitored physical activity levels could be useful to indirectly assess functional recovery.^6^ A recent study in adolescents undergoing spinal fusion found that a majority of participants were characterised by a steep decrease of physical activity after surgery.^7^

Previous research has identified psychosocial risk factors that are associated with the development of CPSP, among them presurgical pain intensity, child anxiety, child pain coping efficacy, child sleep patterns and parental pain catastrophising.^2 8 9^ Generally, emotions and emotion-related factors are known to influence pain, pain-related disability and pain-related distress.^10 11^ There is some research on the role of emotion regulation in chronic pain,^12^ and the role of negative emotions is fairly well documented in the pain experience.^10 13 14^ However, other emotion-related factors such as emotion differentiation and emotion variability have yet to be studied in the context of paediatric CPSP, as they present as good targets for prevention and treatment modules and can be screened for in clinical practice.

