### Objectives

The aim of this observational longitudinal study is to specifically examine the potential role of emotion-related factors (namely emotion variability, emotion differentiation and emotion regulation), as well as familial influences in the development of CPSP and describe pain-related and emotion-related trajectories following major surgery up to 12 months after surgery. We aim to identify whether and which emotion-related factors increase or decrease the risk for the development of CPSP after planned orthopaedic surgery. To the best of our knowledge, this is the first study to specifically examine these emotion-related factors as both potential risk and resilience factors in the development of CPSP.

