Demographics	Age, gender, school, school attendance and performance; family constellation, parental educational level and work status	Parent and self-report: online baseline questionnaire	Parent(s) and child	X				
Medical history	Neonatal intensive care (yes/no), previous surgeries (yes/no; which one), child’s pain history (pain duration, pain location)	Parent report: online baseline questionnaire	Parents	X				
	Complications in the hospital (yes/no) Pain treatment immediately following surgery	Child’s medication list in electronic health record	Data entered by study team		X			
Experience-sampling method	Positive and negative emotions (emotion variability and emotion differentiation)*	Items from the Positive and Negative Affect Schedule^48^	Daily diary: child and parent	X	X			
	Pain severity	Numeric Rating Scale (NRS), 0–10	Daily diary: child	X	X	X		
Psychosocial factors child								
	Pain severity (intensity, distress, interference^77^)*	Numeric Rating Scale (NRS), 0–10	Child self-report				X	X
	Preoperative screening	Paediatric Pain Screening Tool^51 52^	Child self-report	X				
	Functional disability	Functional Disability Index^54^	Child self-report	X	X	X	X	X
	Fear of pain	Fear of Pain Questionnaire^53^	Child self-report	X				
	Pain catastrophising	Pain Catastrophising Scale—three-item version^78^	Child self-report	X				
	Attachment; parent–child relationship	Security Scale^79^	Child self-report	X				
	Symptoms of anxiety and depression*	Revised Child Anxiety and Depression Scale-short version^56^	Child self-report	X	X	X	X	X
	Sleep	Pittsburgh Sleep Quality Index^57^	Child self-report	X	X	X	X	X
	Sensory processing sensitivity	Highly Sensitive Child Scale^58^	Child self-report	X				
	Emotion regulation*	Emotion Regulation Questionnaire—Child and Adolescent version^19^	Child self-report	X				
	Quality of life	Paediatric Quality of Life Inventory^59^	Child self-report	X	X	X	X	X
	Social support	Social Support Questionnaire for Children^60^	Child self-report	X				
	Post-traumatic stress symptoms	Child and Adolescent Trauma Screening^80^	Child self-report	X		X		
Psychosocial factors parents								
	Parents’ own pain history	2 questions: ‘(1) Have you ever and (2) are you currently living with persistent or recurrent pain for at least 3 months?’	Parent self-report	X				
	Postoperative pain measure (child’s pain)	Postoperative Pain Measure for Parents^62^	Parent report		X			
	Fear of pain	Parent Fear of Pain Questionnaire^35^	Parent self-report	X				

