Daily diary—pain and emotions (two time points): At baseline and postassessment, children and adolescents will complete ratings of their pain severity on an 11-point Numeric Rating Scale with anchors 0=‘no pain’ and 10=‘worst pain possible’. Pain severity includes pain intensity, pain-related distress and pain-related interference; hence, participants will give three different ratings.^41 42^ The pain ratings will be used to classify the presence of acute postsurgical pain at the postassessment (in combination with a health-related quality of life rating; see overview of questionnaires for this time point in table 1). In addition, all participants will rate the extent to which they experience positive and negative emotions three times each day on their smartphone and during their normal daily routine over the course of 7 days. These ratings will be used to calculate a score of emotion differentiation (ie, the ability to differentiate between emotional states), a mean value of positive and negative emotions and an index of emotional variability^26 36 37^. The items of the short version of the Positive and Negative Affect Schedule for Children (PANAS-C) will be used to assess emotional state.^38–40^

Daily diary—pain only (once): To diagnose CPSP, participants will be asked to rate their daily pain severity for 7 days starting at FU1. Participants will be prompted at the end of each day to respond on an 11-point numeric rating scale with anchors 0=‘no pain’ and 10=‘worst pain possible’. In addition, daily medication use will be indicated (yes/no and listing medication in a free text field).

Number of steps taken each day will be counted as an indicator of changes in physical activity before and after surgery (ie, at the postassessment), measured by means of accelerometer (GENEActive, Activeinsights), an ambulatory, non-invasive activity-monitoring device that registers physical activity and can be worn around the wrist.

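### The primary CPSP rule takes no account of presurgical status, so children who met it before surgery and still meet it at 3 months count as having developed CPSP

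*Protocol article*

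**What the plan says.** The Primary outcome section states that "The primary endpoint is CPSP at FU 1". The pain half of the rule reads "CPSP is defined as greater than minimal pain (pain intensity ≥3) on more than 50% of days", measured over 7 diary days. The second half is "impairment in health-related quality of life (score of ≤74.9 on the PedsQL"), and the two together give a yes/no variable.

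The Statistical methods section builds the binary variables for acute postsurgical pain and CPSP from the postassessment and FU1 diaries plus quality of life, and defines the two independently. Baseline diary pain is averaged into one mean intensity score per child. It is given no part in the classification.

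The Objectives section asks which "emotion-related factors increase or decrease the risk for the development of CPSP after planned orthopaedic surgery". The Introduction names presurgical pain intensity among the known risk factors. The Eligibility criteria exclude serious comorbidity and prior major surgery, but not existing pain.

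On location, Table 1 lists "child’s pain history (pain duration, pain location") as a parent report at baseline. For FU1, the Procedures section says: "To diagnose CPSP, participants will be asked to rate their daily pain severity for 7 days starting at FU1". It adds a record of medication use and describes no item on where the pain is.

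**The concern.** The study asks what raises or lowers the risk of developing CPSP. A rule that sees only the 3-month state cannot tell a child whose pain began or worsened after surgery from one whose pain and low quality of life were there before and have stayed the same or eased without crossing the thresholds. Both are cases.

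This matters for the predictors of main interest. Emotional state, its variability and its differentiation are measured in the baseline diary week, when any presurgical pain is also present. If existing pain affects those measures and also makes a child more likely to meet the rule at FU1, part of an odds ratio for an emotion measure may describe pain that was already there. The risk score would likewise be partly a score for persistence, and readers would take it as a score for onset.

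**Working it through.** **1. What each element of the rule refers to**

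- Pain: intensity of at least 3 on more than half of 7 days. Since 3/7 = 43% and 4/7 = 57%, this means at least 4 days. Time point: FU1. Reference to baseline: none.
- Quality of life: PedsQL of 74.9 or less, a fixed cut-off from normative data. Time point: FU1. Reference to baseline: none. The scale is generic and is not tied to the operation.
- Link to acute pain: none, because the two states are defined independently.
- Link to the operated area: none described.

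Take a child who meets both criteria at baseline and at FU1. Under the Primary outcome section this child is a CPSP case, whichever way the scores moved in between.

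**2. Does the planned model deal with this?**

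The primary model takes the starred variables of Table 1. The diary pain row that is ticked at baseline has no star. A separate pain severity row is starred, but its ticks stand at FU2 and FU3 only. Statistical methods also says that baseline variables enter the prediction model and that multi-day measures are averaged. Baseline pain may therefore be intended as a predictor, but the text does not settle it. If it is included, the emotion effects become conditional on baseline pain, but the outcome label stays the same.

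**3. The plan's own sizing**

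Inputs from the sample size section: 280 dyads, 25% CPSP, 10 events per variable (EPV).

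- Events: 280 × 0.25 = 70
- Predictors: 70 / 10 = 7

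The figures reproduce exactly and leave no reserve.

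**4. What a restriction to new cases would leave**

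The documents give no rate of presurgical rule-positive children, so the share *s* of the 70 cases already present is an assumption. Events left = 70 × (1 − s).

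| Assumed share s | Events left | Predictors at 10 EPV | EPV if all 7 are kept |
|---|---|---|---|
| 10% | 63 | 6 | 9 |
| 20% | 56 | 5 | 8 |
| 30% | 49 | 4 | 7 |
| 40% | 42 | 4 | 6 |
| 50% | 35 | 3 | 5 |

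To see what lies behind a given *s*, let *b* be the proportion meeting the rule at baseline and *q* the proportion of these who still meet it at FU1. Cases already present = 280 × b × q, with the total held at 70.

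- b = 5%, q = 50%: 7 cases, 7/70 = 10%
- b = 10%, q = 50%: 14 cases, 14/70 = 20%
- b = 20%, q = 50%: 28 cases, 28/70 = 40%

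These lines show how strongly the result depends on *b* and *q*. They are not estimates for this population.

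**The case against.** Several counter-arguments carry weight.

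- **The rule is not about pain alone.** A reader might infer that any pain at 3 months, such as a headache, makes a case. It does not: the pain must be present on at least 4 of 7 days and PedsQL must be 74.9 or less. This stands and narrows the problem. It does not remove it, because the PedsQL half also ignores the baseline score.
- **The article does not promise incident cases only.** In the Introduction CPSP "is defined as chronic pain that persists over time (at least 3 months) following a surgical procedure", and the sample size section speaks of a prevalence. The article also cites earlier research and a modified international definition in support of its rule. Those sources are not at hand and cannot be tested here. This is why the primary definition should be kept. The tension is with the Objectives, which speak of development after surgery.
- **A risk score may validly predict persistence.** True for prediction. But the article also wants to identify factors that increase or decrease risk, and there the distinction matters.
- **Bias in the emotion effects is not demonstrated.** A reader might infer that reverse causation inflates these odds ratios. The documents show neither that it occurs nor in which direction. The Introduction treats habitual emotion regulation as stable within individuals, which makes the mechanism less plausible for that predictor than for the diary-based measures.
- **A condensed article need not list every diary item or sensitivity analysis.** Correct. The absence of a site question at FU1 is an inference from silence and cannot be stated as fact. The classification rule itself, however, is stated as settled.

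**Conclusion.** The point holds in a limited form. As written, the primary rule makes no reference to presurgical status, so children who meet both criteria before surgery and again at FU1 are counted as having developed CPSP. Associations with baseline emotion measures could partly reflect existing pain, and the article does not clearly place baseline pain in the primary model.

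The size cannot be derived from the documents. A reader might infer from the arithmetic that a large part of the 70 cases is pre-existing, but any such share rests on two assumed rates, and nothing in the article supports a particular value. What can be said is that the sizing has no slack: 70 events support exactly 7 predictors at 10 EPV, so an analysis restricted to new cases falls below 10 EPV for that set as soon as one case is set aside.

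This is a question of how the outcome matches the objective. The sample size arithmetic is correct.

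**What to change.** Keep the primary definition, and with it comparability with the research the article cites. In the statistical analysis plan, which the article says is finalised before data export:

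1. Apply the same two criteria to the baseline diary and baseline PedsQL. The abstract describes baseline diaries completed three times a day, whereas the FU1 diary has one end-of-day prompt. State how several baseline ratings are reduced to one daily value comparable with the FU1 rating.
2. Report CPSP cases at FU1 split by whether the child met the rule at baseline.
3. Name mean baseline pain intensity explicitly as a predictor in the primary model, within the budget of 7.
4. Prespecify a supportive analysis restricted to children who did not meet the rule at baseline, with a reduced predictor set named in advance.
5. Optional, if the full diary does not already have it: one yes/no item at FU1 on whether the pain is in the operated area.

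**Cost.** Items 1 to 4 need wording only, since the data are already being collected. Item 3 uses one of the 7 predictor places. Item 4 has fewer events: with 20% of cases pre-existing, 56 instead of 70, which supports about 5 predictors. Item 5 adds one question per diary evening and helps only children who have not yet reached FU1.

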### Secondary outcomes

Secondary endpoints are trajectories of pain and emotion-related factors over time (ie, baseline through FU3), number of steps taken by patients, pain severity and quality of life. Postoperative complications will be monitored using the modified Clavien-Dindo Classification.^70^

### Statistical methods

Descriptive statistics will include mean and SD or median and IQR for normally distributed and non-normally distributed or ordinal variables measured at baseline. Categorical variables will be reported as number and percentage of total. The primary outcome is binary, therefore, generalised linear regression models or generalised linear mixed effects models will be used, using a logit link function. Fixed effects will be estimated for the primary predictors (as marked in table 1). Random effects will be included in the longitudinal model to account for repeated observations in the individual participants. The resulting estimands will be ORs and 95% CIs. Variables at baseline will be used in the prediction model, with performance measures area under the curve, calibration and scaled Brier Score.^71 72^ Variables measured consecutively over multiple days at each assessment interval will be averaged over time. We will use the rule of 10 EPV that would determine the number of independent variables in the regression model. Potentially time-varying covariates will be addressed. Potentially non-linear relationships of the independent variables with outcome will be evaluated. Further, the purpose of the multivariable regression analysis is to develop a risk score for CPSP. This will allow to identify variables that increase or decrease the risk for CPSP, by combining them into a multivariable model.

The preselected variables (ie, the primary predictors) will be assessed for collinearity with pair-wise scatter plots, pair-wise interaction terms will be included successively into the model. For the preselected variables, no variable selection will be performed. In an exploratory analysis, potential other variables will be evaluated and the process will be described in more detail in the statistical analysis plan.

Any missing values in the independent variables or the outcome will be addressed with 100-fold multiple imputation, using chained equations. Resulting estimates will be pooled using Rubin’s rule.^73 74^

We will conduct bivariate analyses to compare study completers vs study dropouts to detect potential differences regarding participant demographic between the groups. Baseline daily pain ratings will be averaged for each participant to calculate a mean baseline pain intensity score. Postassessment and FU 1 daily pain ratings will be combined with health-related quality of life data to define binary outcome variables for acute postsurgical pain and CPSP. Acute postsurgical pain and CPSP will be defined independently.

For the trajectory analysis, the classification method K-means for longitudinal data will be used to determine clusters in the data (R package kml).^75^ The analysis of clusters joint trajectories (R package kml3d)^75^ will be applied, as this analysis allows summarising several correlated continuous variables into a single nominal variable.^76^ The trajectory analyses will be considered exploratory. Alternative clustering methods would be based on the risk score and participants with high risk for developing CPSP can be identified based on a cut-off of 10% predicted probability.

A detailed statistical analysis plan will be written up and finalised before data export for analysis. All analyses will be performed with the R programming language in a fully scripted way and dynamic reporting will be used to guarantee highest level of reproducibility.

### Monitoring

The study will be monitored for quality and regulatory adherence. The monitor, who is not involved in our study and supervised by the Clinical Trials Centre of the University Hospital Zurich, Switzerland, will ensure that the specifications of the project plan and the associated processes are adhered to.

## Ethics and dissemination

The Ethics Committee of the Canton of Zurich, Switzerland, has approved the study and all study-related procedures including the consent procedures for minors under the age of 18 years (ID: 2023-01475). All participants will be compensated for their time by means of a voucher. We will reimburse participating families per assessment time point, so that families who drop out will still receive a certain amount of compensation. The first few participating families will be asked about general accessibility of the study. Their feedback will be implemented in study procedures if necessary.

The risk of adverse effects due to the study is considered to be minimal. All project data will be handled with the uttermost discretion and will only be accessible to the study team. Data will be stored on a secured and password-protected server.

This study is registered at ClinicalTrials.gov (identification number: NCT05816174). After study completion, the study team organises a dissemination workshop aiming at youth with CPSP and their parents, researchers, clinicians and the interested public, to discuss study results, clinical implications, and formulate future research questions.
